### Laboratory Procedures

#### Gut Colonization

Rectal swabs and stool samples will be tested for the presence of the probiotic species and strains used in this study using quantitative polymerase chain reaction (qPCR). Assays will be performed at the PNGIMR using an in-house method developed and optimized for local laboratory conditions. Briefly, total DNA will be extracted from approximately 200 mg of stool or 600 to 800 µL of rectal swab eNat preservation medium using the FastDNA Spin Kit for Soil (MP Biomedicals), incorporating a bead*-*beating step to enhance bacterial cell wall disruption.

Singleplex qPCR reactions will be used to detect *B longum* subspecies *infantis* and *L plantarum*, using the TaqMan Fast Advanced Master Mix (Thermo Fisher Scientific). Standard curves will be generated from DNA extracted from quantified cultures of *B longum* subspecies *infantis* and *L plantarum* grown either at the PNGIMR or at Federation University, Australia.

The primer and probe sequences to be used for *B longum* subspecies *infantis* are as follows:

Bi26_Forward 5 - GTCACGATGTCTCCTTTGATATCA GCATG-3′Bi26_Reverse 5′- CCTTTTGCGTCTCCCCCG-3′Bi26_Probe 5 - FAM-TCATTCATTGTAGTGGCGATCAC CGTTACC-3′

The primer and probe sequences to be used for *L plantarum* are as follows:

Lp_Forward 5′-ACAAATGGCAGGGCGAAAAATG-3′Lp_Reverse 5′-TTCTACATCCGGGCAAACCTTG-3′Lp_Probe 5′- FAM-ACGGAGCTTCTATGACGATGCTT TCA-3′

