### Sample Size Calculation

It was determined that a sample size of 50 participants per group would achieve 90% power to detect a difference in colonization rates of 30% in the probiotic group versus 5% in the placebo group, using a 2-tailed test of proportions with continuity correction at the 5% significance level. A final sample size of 65 participants per group was decided upon, taking into account a presumed 10% loss to follow-up and difficulties in timely biosample collection. On the basis of this sample size, it was estimated that the study would have 80% power to detect a 50% reduction in pneumococcal colonization rate in the probiotic group versus the placebo group at the 5% significance level.

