### Statistical Analyses

The data will be cleaned before analysis. All data will be downloaded from REDCap and a backup copy archived before data cleaning. Missing data, outliers, and inconsistencies will be queried and verified against source documentation. Where data require changing, the database will be updated accordingly. All queries and corresponding amendments will be documented. Per-protocol and intention-to-treat analyses will be performed using available outcome data. The distribution of missing data across the treatment groups will be described, and reasons for missingness will be explored where possible to assess whether data are missing at random.

The primary objective is to determine the feasibility and safety of treatment. The number of solicited and unsolicited adverse events as well as the number of discontinued, missed, and completed doses will be summarized descriptively by treatment group. Pearson chi-square and Fisher exact tests will be used as appropriate to determine the significance of differences between groups.

The secondary objective is to measure gut colonization by probiotic strains on the last day of treatment (d 7-d 10) and at ages 1, 3, and 4 months. The prevalence of colonization at each time point will be summarized descriptively by treatment group. Colonization status, categorized as positive or negative, will be compared between treatment groups using the Pearson chi-square test, while continuous measures of colonization (ie, cycle threshold or relative fluorescence units) will be analyzed using 1-way ANOVA.

The exploratory objectives include measuring the hospitalization rates throughout the study; nasopharyngeal carriage of *S pneumoniae* and other respiratory bacteria; IgG antibody titers to PCV13, DTwP, Hib, and hepatitis B; the kinetics of probiotic gut colonization; and maternal carriage of probiotic species at the time of delivery.

Hospitalization rates will be reported descriptively per treatment group and compared using Pearson chi-square or Fisher exact tests as appropriate.

Nasopharyngeal carriage of *S pneumoniae* and other respiratory bacteria as well as gut colonization will be summarized descriptively at each corresponding time point. A Cox regression analysis will be performed, adjusting for birth weight, sex, previous antibiotic use, and breastfeeding status. Hazard ratios, along with their 95% CIs and *P* values, will be reported.

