## Results

### Assent and Enrollment

A total of 244 children were enrolled between October 29, 2020, and June 30, 2023, and randomly assigned to receive *L plantarum* (ATCC 202195), *B longum* subspecies *infantis* (Bi-26), or placebo (maltodextrin). Figure 2 shows the number of women who provided assent, the number of infants randomly assigned, the number of children seen at subsequent visits, and the number of early terminations. Reasons for participant loss between maternal assent and infant screening were not systematically recorded; informal observations suggest that this was primarily due to early postnatal discharge, family disagreement after providing assent, or change of mind. In the first year of the study, only 63 (32.3%) of the target 195 infants were enrolled. This shortfall was largely due to the onset of the COVID-19 pandemic, which led to multiple government-imposed lockdowns and curfews that restricted field activity and hindered recruitment efforts. However, recruitment increased during the second year, and by the end of December 2022, the full cohort of 195 participants had been recruited. Nearly half of these participants (94/195, 48.2%) were enrolled between March and the end of June 2022 (Figure 3).

We had a higher-than-anticipated loss to follow-up because participants’ families left the study area during the study period, largely owing to the COVID-19 pandemic; hence, at the end of March 2023, we obtained ethics approval to recruit an additional 45 participants. This increased the target sample size from 195 to 240 (n=80 per treatment group). These additional participants were enrolled between April and June 2023 (Figure 3).

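### One-way ANOVA on cycle threshold or fluorescence does not suit a measure that, at the plan's own colonization rates, is undetected in most samples

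*Protocol article*

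**What the plan says.** The Statistical Analyses section of the protocol article treats gut colonization in two ways. Positive/negative status is compared between groups by Pearson chi-square. Separately, "continuous measures of colonization (ie, cycle threshold or relative fluorescence units) will be analyzed using 1-way ANOVA". The section does not say how a sample without amplification enters the ANOVA, and it bases the analyses on available outcome data.

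Three other places bear on this:

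- **Sample Size Calculation** plans for "a difference in colonization rates of 30% in the probiotic group versus 5% in the placebo group".
- **Laboratory Procedures, Gut Colonization** runs a separate (singleplex) qPCR for each species, and "Standard curves will be generated from DNA extracted from quantified cultures".
- **Statistical Analyses, later paragraph on normality** calls for normality tests and histograms before parametric testing. The only remedy it names is log transformation.

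**The concern.** The test and the variables are named, and they do not fit what the design expects to see. If colonization is near the planning rates, most samples in each assay will be negative. ANOVA can then be run on cycle threshold in only two ways, and neither answers the question well.

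- **Detected values only.** Infants are included because of something that happened after randomization. A few carriers in the non-target arms are compared with a larger group of colonized infants in the target arm.
- **All infants, with a filled-in ceiling.** The data become a large spike at one value plus a scatter of real readings. Group means and variances then depend on where the spike is placed.

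On relative fluorescence a value can exist for every sample, so nothing need be missing, but the negatives still form a cluster at background. At stake is whether the load comparison reflects the trial's data or a coding choice that the article does not state.

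**Working it through.** **1. The plan's own figure.** Inputs from Sample Size Calculation: 30% v 5%, two-sided 5%, 90% power, continuity correction, 50 per group. With unpooled variance:

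n = (1.960 + 1.282)² × (0.30×0.70 + 0.05×0.95) / 0.25² = 43.3

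With continuity correction: n/4 × (1 + √(1 + 4/(n×0.25)))² = 51.0, so 51 per group. Power at 50 is 89.3%. The stated "a sample size of 50 participants per group would achieve 90% power" is reproduced to within one infant per group, so 30% and 5% are the rates that the design rests on.

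**2. Share of non-detects.** Target arm: 1 − 0.30 = 70%. Placebo: 1 − 0.05 = 95%. The article gives no rate for a strain in the other synbiotic arm. Assuming 5% there too:

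1 − (0.30 + 0.05 + 0.05)/3 = 86.7% per assay

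Range over other assumed rates:

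| Target arm | Each other arm | Non-detects over three arms |
|---|---|---|
| 30% | 5% | 87% |
| 30% | 30% | 70% |
| 80% | 5% | 70% |
| 100% | 5% | 63% |
| 100% | 30% | 47% |

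Of these cases, non-detects stop being the majority only with full colonization of the target arm and high background carriage.

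**3. Detected values only.** Expected positives are 0.30n in the target arm and 0.05n in each other arm. The chance that a 5% arm has fewer than two positives is q = 0.95ⁿ + n×0.05×0.95ⁿ⁻¹. The chance that this happens in at least one of two such arms is 1 − (1 − q)².

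| n per arm | Source | Expected positives | q | At least one arm |
|---|---|---|---|---|
| 59 | 178 infants at 4 months (Table 1) / 3 | 17.7 v 2.95 v 2.95 | 20% | 36% |
| 65 | final planned size | 19.5 v 3.25 v 3.25 | 16% | 29% |
| 80 | expanded target | 24 v 4 v 4 | 9% | 16% |

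**4. Filled-in ceiling.** Simulated one-way ANOVA, 65 per arm, 20,000 trials per setting. The cycle-threshold means, SDs and fill-in values are assumptions, not figures from the article.

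| Scenario | Fill-in 36 | Fill-in 40 | Fill-in 45 |
|---|---|---|---|
| A: prevalence 30/5/5%, mean 32 in target-arm positives v 26 in the others, SD 3 | 42% | 81% | 92% |
| B: prevalence 30% in all arms, mean 26 v 30 v 30, SD 4 | 36% | 20% | 13% |

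The reason shows in the expected means for scenario A. With a fill-in f, the target arm averages 0.30×32 + 0.70f and the others 0.05×26 + 0.95f. The gap is 0.7 cycles at f = 36, 1.7 at 40 and 2.95 at 45. The same infants give a different effect according to f. In B, where load truly differs, a higher ceiling hides the difference; ANOVA among positives alone rejects in about 88% of trials.

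**5. The normality safeguard.** For one arm of 65 with 30% positive (assumed mean 28, SD 4, fill-in 40), Shapiro-Wilk rejected in all 500 simulated samples, both raw and after log transformation. A transformation moves the spike but leaves it a spike.

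**The case against.** The strongest reply has four parts.

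- **The colonization difference is already tested.** The same sentence compares positive/negative status by chi-square. At 30/5/5% and 65 per arm, the three-arm chi-square rejects in about 99% of simulated trials. A reader might infer that the ANOVA could hide a real difference in colonization. The article does not support that, because prevalence is the chi-square's task. If colonized infants carry the same load in every arm, an ANOVA among positives that rarely rejects is behaving correctly. With a filled-in ceiling (mean 32 in all positives, SD 3, 75 per arm) ANOVA itself rejects in about 95% of trials or more. This part stands in full.
- **The rates are assumptions.** No colonization results are reported, the 30% and 5% carry no time point, and the first analysis is on the last day of dosing. Some samples called negative may show a late cycle threshold. This stands as a caveat, and the range in step 2 shows how far it reaches.
- **Fluorescence is not missing.** A reader might infer that about 87% of values are absent on both measures. That holds for cycle threshold only.
- **Handling of non-detects and pairwise contrasts belongs in the SAP, which is not shown.** This is partly right: the fill-in rule and the follow-up to a three-arm F test could be set there. But the article itself fixes ANOVA on raw cycle threshold or fluorescence, and no fill-in rule makes that a good fit. The normality check would probably flag the problem, but its one named remedy does not solve it.

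**Conclusion.** The point holds as a poorly fitting stated method, confined to the quantitative part of the secondary objective. At the planning rates 70% of the target arm and 95% of placebo are non-detects, and about 87% per assay if the other synbiotic arm also sits at 5%. Under the assumed loads, the rejection rate moves between about 42% and 92% on the fill-in value alone. A detected-only analysis at 65 per arm would leave a 5% arm with fewer than two positives in about 29% of trials.

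A reader might go further and call the quantitative results uninterpretable. The article does not support that: a stated rule and a suitable model would make them usable, and the chi-square is untouched. The primary aims, feasibility and safety, are not affected. The change should be made, but nothing in the trial's main conclusions depends on it.

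**What to change.** Replace the ANOVA on raw cycle threshold or fluorescence with an analysis of log10 quantity read from the standard curves already planned. For each assay, compare that strain's target arm with placebo by one of the following, named in advance:

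- a left-censored (Tobit) model with censoring at the assay detection limit; or
- a Wilcoxon rank test with non-detects tied at the lowest rank.

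Report load among colonized infants descriptively, with the number of positives in each arm.

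The rule should be fixed before unblinding, that is, before colonization data are seen by arm. The article already gives dose completion by named arm, so if allocation is open to the analysts, the change should be dated and disclosed.

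The cost is a change of wording and a little more analysis work, with no new samples or assays. Each option has a limit. The rank test will largely reflect prevalence and so overlaps with the chi-square. The censored model leans on its distributional assumption where few values are detected, as in placebo.

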### Specimen Collection

For the secondary and exploratory objectives of the study, a number of biological samples were collected at several time points throughout the study (Figure 1). Rectal swabs and stool samples were collected to assess intestinal colonization by probiotic species. Rectal swabs were collected at enrollment; on the day of the last intervention administration (age 7-10 d); and at ages 2 weeks, 1 month, 3 months, 4 months, and 6 months. For sample collection, the infant was carefully placed face down across the mother’s thighs. A FLOQSwab (Copan Diagnostics) was gently inserted approximately 2 cm into the anal canal, rotated slowly for 10 seconds, then removed and placed into a tube containing eNAT preservation and transport medium (Copan Diagnostics). The swab was broken at the breakpoint, leaving the tip in the tube, which was then sealed and mixed by inverting 10 times. Stool samples were collected in addition to rectal swabs if infants passed stool during the study visit to allow for sensitivity comparisons of probiotic strain detection in rectal swabs versus stool. Stool samples were taken from infants’ diapers using a scoop and placed into stool specimen containers for storage and transportation. Upon arrival at the PNGIMR laboratory, stool samples were transferred to cryovials by laboratory staff. Both rectal swabs and stool samples were then stored at −80 °C.

Nasopharyngeal swabs to assess bacterial carriage and load were collected at ages 2 weeks, 1 month, and 4 months using FLOQSwabs. At each time point, 2 swabs were collected per infant when possible. For each collection, a swab was inserted horizontally into the nostril to collect a superficial mucosal sample from the anterior nares, advancing gently until resistance was met. The swab was then rotated while counting to 5 (or for approximately 3 s) before being removed. One swab was placed in skim milk tryptone glucose glycerol broth (STGGB) for culturing of bacterial pathogens (priority), and the second was stored in PrimeStore molecular transport medium (Thermo Fisher Scientific) for deep sequencing. Both samples were stored at −80 °C.

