### Follow-Ups and Early Study Terminations

Of the 244 enrolled infants, 169 (69.3%) successfully completed the study by December 2023. Among the 75 early study terminations, 37 (49%) infants were lost to follow-up, 28 (37%) infants’ families moved out of the study area before study completion, and 9 (12%) infants’ parents withdrew consent. Moreover, of these 75 participants, 1 (1%) was withdrawn by the physician for medical reasons not related to the study intervention. The majority of these early terminations (59/75, 79%) occurred after the 1-month visit (Figure 2).

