### Protocol Violations

There were no protocol violations; however, there was 1 incident of an accidental delivery of the study intervention to a nonstudy participant. This child was monitored over several days by study staff to ensure their well-being, and the parents were informed to contact a member of the study team in the event of any illness. No adverse events were subsequently reported for this child.

In addition, during July and August 2023, there was a shortage of routine vaccines in Goroka, which delayed some of the follow-up visits and specimen collections for 45 (18.4%) of the 244 study participants. Regarding the birth dose vaccines, 11 (4.5%) of the 244 participants did not receive hepatitis B, and 15 (6.1%) did not receive BCG; 5 (2%) received neither hepatitis B nor BCG, with 4 (80%) of these participants subsequently lost to follow-up before the 1-month visit. Of the 244 participants, 24 (9.8%) experienced delays in receiving BCG, with 14 (58%) of these participants receiving it 2 to 3 months after birth.

Among the routine monthly vaccination visits, delays were observed as follows: 7 (2.9%) of the 244 participants had their 1-month vaccines delayed, 11 (4.5%) had their 2-month vaccines delayed, and 4 (1.6%) had their 3-month vaccines delayed. For participants with a delayed monthly vaccination visit, the timing of all subsequent scheduled follow-up visits for sample collection and vaccination were readjusted accordingly; for instance, if a participant’s 1-month vaccines were delayed by 24 days, their 2- and 3-month vaccines were also delayed by 24 days. Of the 22 participants with delayed monthly vaccinations and sample collections, 3 (14%) were subsequently lost to follow-up: 1 (33%) before receiving their 1-month vaccinations and 2 (67%) before receiving their 3-month vaccinations. No participant remaining in the study experienced >1 additional delayed monthly vaccination.

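### Cox regression is the only between-arm analysis named for nasopharyngeal carriage, a reversible state swabbed at three ages, so its hazard ratio does not estimate carriage at each age

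*Protocol article*

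**What the plan says.** Under Study Design and Objectives, the exploratory carriage objective is nasopharyngeal carriage at three named ages, and hospitalization is followed to 6 months. Specimen Collection gives the sampling: "Nasopharyngeal swabs to assess bacterial carriage and load were collected at ages 2 weeks, 1 month, and 4 months using FLOQSwabs". Rectal swabs were taken at enrollment, on the last dosing day, "and at ages 2 weeks, 1 month, 3 months, 4 months, and 6 months".

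Statistical Analyses says that nasopharyngeal carriage "as well as gut colonization will be summarized descriptively at each corresponding time point". The next sentence is "A Cox regression analysis will be performed, adjusting for birth weight, sex, previous antibiotic use, and breastfeeding status", followed by the effect measure: "Hazard ratios, along with their 95% CIs" and P values. No event, time origin or handling of clearance is given.

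Gut colonization is also the secondary objective. There it has its own Pearson chi-square test between arms on the last dosing day and at 1, 3 and 4 months, and an ANOVA of the continuous measures.

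For admissions: "Hospitalization rates will be reported descriptively per treatment group and compared using Pearson chi-square or Fisher exact tests as appropriate". On exits, Follow-Ups and Early Study Terminations reports 75 of 244 infants leaving early and says: "The majority of these early terminations (59/75, 79%) occurred after the 1-month visit". The Figure 2 caption reports no substantial difference in completion between groups.

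**The concern.** A Cox model suits an event that happens at a known time. Nasopharyngeal carriage is a state that an infant can enter, leave and re-enter. With swabs at three ages, none at enrollment and none between 1 and 4 months, the onset date is never seen. All onsets fall on a few shared dates, and an infant who acquired and cleared between two visits looks never to have carried.

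Visit timing also enters the estimate. After a delayed vaccination, "the timing of all subsequent scheduled follow-up visits for sample collection and vaccination were readjusted accordingly", so actual ages at swabbing vary and a late swab can be read as late acquisition.

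What is at stake is the answer to the trial's own question. The objective asks how many infants carry at each age, and the Sample Size Calculation speaks of a 50% reduction in a colonization rate. The descriptive summaries give the proportions, but the only inference between arms would be on a hazard ratio with no defined event.

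Admissions raise a smaller issue. Daily ward monitoring allows them to be dated, yet the named test uses no follow-up time although almost a third of infants left early.

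**Working it through.** **The article's own figures**

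- Early exits: 75/244 = 30.7%, and 1 − 169/244 = 30.7%. Exits after the 1-month visit: 59/75 = 79%. Both agree with the text.
- Power for carriage, 65 per arm, two-sided 5%, halving of the rate. The base rate is not stated. At 45% in placebo the power is 78%, and at 50% it is 85% (80% with continuity correction). The stated 80% therefore matches a comparison of proportions with roughly 46 to 50% carriage in placebo. It is not a hazard-ratio calculation.

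**What the hazard ratio would measure**

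The document gives no acquisition or clearance rates, so these are assumed. Each infant starts uncolonized, acquires at rate λ and clears at rate μ per month, and is seen only at 0.5, 1 and 4 months. Carriage at age t is

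p(t) = λ/(λ+μ) × [1 − exp(−(λ+μ)t)].

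Placebo with λ = 1 and μ = 0.5 gives p(4) = 0.667 × (1 − e^−6) = 0.67. Cox was fitted to the first positive swab, with 20,000 simulated infants per arm. That event is an assumption, because the article defines none.

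| Effect of intervention | Carriage at 0.5, 1, 4 mo (placebo 35%, 52%, 67%) | HR, Efron ties | HR, Breslow ties |
|---|---|---|---|
| Acquisition halved | 20%, 32%, 49% | 0.56 | 0.62 |
| Clearance doubled only | 32%, 43%, 50% | 0.81 | 0.86 |
| Clearance tripled only | 28%, 37%, 40% | 0.68 | 0.74 |

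Rows 1 and 2 end with almost the same 4-month carriage, but their hazard ratios are 0.56 and 0.81. Row 3 has the lowest 4-month carriage, yet a weaker hazard ratio than row 1. With μ varied from 0.1 to 2, a true acquisition ratio of 0.50 is estimated at 0.53 to 0.56 (Efron) or 0.57 to 0.66 (Breslow).

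**How much is due to ties alone**

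If carriage is treated as permanent once acquired (60 per arm, true ratio 0.50, three acquisition levels), Breslow gives 0.549, 0.571 and 0.597. Efron gives 0.501, 0.496 and 0.516, and a discrete-time complementary log-log model 0.496, 0.483 and 0.501. Ties are therefore a software-dependent nuisance. Reversibility is the substantive problem.

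**Admissions**

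Infants in follow-up, from Table 1: 244, 234, 227, 226, 196, 178 and 169 at 0, 0.3, 0.5, 1, 3, 4 and 6 months (0.3 stands for the 8-10 day visit). The trapezoid rule gives

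71.7 + 46.1 + 113.25 + 422 + 187 + 347 = 1187 infant-months,

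against 244 × 6 = 1464 planned, or 81%.

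With constant hazard and this exit pattern, assumed true 6-month risks of 10%, 20% and 30% appear as 8.2%, 16.2% and 24.5% when all enrolled infants form the denominator. That is about 18 to 19% too low.

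The contrast behaves differently. With 81 per arm and equal exits:

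- The chi-square test has type I error of 4.2 to 5.3%.
- A true rate ratio of 0.50 gives a crude risk ratio of 0.51 to 0.53.
- Power is within about 2.5 points of a person-time test (for example 46.0% against 48.4%).

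Only with unequal exits does the contrast shift. At an assumed 20% against 40%, a null effect gives a crude risk ratio of about 0.85 and type I error of 6 to 9%.

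**The case against.** Several stronger readings are tempting, and the document does not support them.

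- **That the admission comparison misleads.** The reported completion is similar across arms, and with equal exits the chi-square contrast is nearly unaffected. The plan also describes missingness by arm and explores its reasons. The understated absolute rate arises only if all enrolled infants form the denominator, and the article says only that available outcome data are used. Censoring at exit would itself assume that leaving is unrelated to admission risk.
- **That per-visit questions on gut colonization go unanswered.** They are covered by the chi-square tests at the end of dosing and at 1, 3 and 4 months. Two arms with equal early detection but different persistence could give a hazard ratio near 1, but the later tests would show the difference.
- **That Cox turns a true 0.50 into 0.55 to 0.60 through ties.** This holds only under Breslow. Efron is close to 0.50 when carriage is permanent, and the article names no tie method.
- **That the plan fixes first detection as the event and discards later swabs.** That is an inference, because no event is stated. A full analysis plan may define one and may handle interval censoring.

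The last argument is the strongest. It does not remove the point, because the choice of Cox and hazard ratios is stated text, and better definitions would still not turn a hazard ratio into carriage at each age. It is also fair that nasopharyngeal carriage, colonization kinetics and hospitalization are exploratory outcomes of a pilot whose primary objectives are safety and feasibility.

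**Conclusion.** The concern holds for nasopharyngeal carriage. The stated model does not match the stated objective or the power statement, and no other between-arm comparison is named for this outcome. Under the assumed rates, the hazard ratio can be 0.56 or 0.81 for nearly the same 4-month carriage, and an effect on clearance alone gives about 0.7 to 0.8 (0.68 to 0.86 across both tie methods). These sizes rest on a constant-rate two-state model, no carriage at birth and a first-positive event. The direction of the argument needs only that carriage is reversible and seldom observed.

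For gut colonization the change is a refinement. For admissions, the finding is limited to the absolute 6-month rate, which is understated by roughly 18 to 19% if all enrolled infants are the denominator. It matters because the pilot is meant to inform a larger trial. Bias in the between-arm test is not shown.

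Severity: should fix, since the affected analyses are mainly exploratory.

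**What to change.** 1. Nasopharyngeal carriage: replace Cox with a repeated-measures binary model (GEE or mixed logistic) with arm, visit, arm-by-visit and the covariates already listed. Report each synbiotic arm against placebo at 2 weeks, 1 month and 4 months with 95% CIs. Numbers fall from 226 at 1 month to 178 at 4 months, so state the missing-data assumption; ordinary GEE needs a stricter one than a likelihood-based mixed model.
2. If time to first acquisition is also wanted, define the event and time origin, use actual ages at swabbing, and fit an interval-censored or discrete-time complementary log-log model.
3. Gut colonization: keep the planned chi-square tests. Use the same repeated-measures model in place of Cox for the kinetics objective, so that all sampled visits contribute.
4. Admissions: report events per person-time, or time to first admission censored at exit, and state the denominator. The chi-square or Fisher test may stay beside it.

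The cost is revised analysis wording and modest extra modelling. No new data are needed, and the article says that analysis was still in progress.
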